**Baseline risk**							
**(Year 1)^**	**Relative risk reduction**						
	**10%**	**15%**	**20%**	**25%**	**30%**	**35v**	**40%**
**15.5%**	14.5%	28.5%	48.1%	69.3%	**86.3%**	**95.7%**	**99.2%**

*Number of patients per treatment arm, alpha = 0.05.

^Year 2 risk is 27.2%.

Bold numbers indicate statistical power range for this study.

While the revised assumptions based upon data collected from the first 589 patients to complete follow-up differ from the initial assumptions, the event annual rate of revision surgery of 15.5% in year 1 and 27.2% in year 2 are well within the range of 0-44% that have been previously reported in the literatures [39-41].

### Statistical methods

#### *Primary analysis*

All outcome analyses will adhere to the intention to treat principle. To evaluate the effect of sliding hip screw versus cancellous screws in time to revision rates, a Cox proportional hazards model will be used with the following covariates that are included in the minimization procedure: (1) Age (50–80 years or >80 years (81 years or older)); (2) Undisplaced or displaced femoral neck fractures; (3) Pre-fracture living setting (i.e., institutionalized or not institutionalized); (4) Pre-fracture functional status (i.e., using ambulatory aid or independent ambulator); (5) American Society for Anesthesiologists (ASA) Class (i.e., Class I/II or III/IV/V); and (6) Clinical site.

The treatment effect will be evaluated using a likelihood ratio test, and the validity of the proportional hazards assumption of the Cox model will be assessed. Survival rates at each follow-up period will be compared and then the overall difference between survival curves with log-rank tests will be evaluated, adjusting for the covariates. Absolute revision rates, risk reduction, absolute risk reduction, and the number needed to treat with screws and sideplate will be calculated. All results will be presented with 95% confidence intervals.

#### *Secondary analysis*

We will also examine the relative effect of sliding hip screw versus cancellous screws on time to mortality, avascular necrosis, nonunion, implant breakage or failure, time to fracture healing, and infection (i.e., superficial and deep) using Cox proportional hazards modeling. The treatment effect will be evaluated using a likelihood ratio test, and the validity of the proportional hazards assumption of the Cox model will be assessed. Survival rates at each follow-up period will be compared and the overall difference between survival curves with Log-Rank tests will be evaluated. Absolute revision rates, risk reduction, absolute risk reduction, and the number needed to treat with screws and side plate will be calculated. All results will be presented with 95% confidence intervals.

#### *Subgroup analyses*

We plan to conduct a single subgroup analysis comparing the effects of multiple screws versus sliding hip screw in patients with undisplaced and displaced femoral neck fractures. All analyses will be adjusted for important determinants of outcome (the prognostic variables outlined in the randomization section). The analysis plan is to fit logistic regression models and include treatment by subgroup interactions to assess whether the magnitude of the treatment effect is significantly different between subgroups. The survey and population-based data from Sweden suggests that two-thirds of all included fractures will be displaced [48]. Thus, approximately 1,000 displaced fractures (500 per group) and 500 undisplaced fractures (250 per group) can be expected. The weighted risk of revision in displaced fractures is 30.2%, (95% CI = 24.1, 6.4) and 20.4% (95% CI =17.4, 23.4%) in undisplaced fractures. The power tables suggest that the study will be able to detect relative risk reductions of 30% or greater with sliding hip screw compared to multiple cancellous screws in displaced fractures (Table 4).

**Table 4 T4:** Displaced fractures: estimated study power for 500 patients per treatment arm (N = 1,000)

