### Study outcomes

#### *Primary study endpoints*

The primary study endpoint is re-operation within 24 months post initial surgery to promote fracture healing, relieve pain, treat infection, or improve function including the following: (1) Implant removal prior to fracture healing; (2) Revision surgery with another internal fixation implant; (3) Revision surgery to arthroplasty; and (4) Soft tissue procedures, especially incision and drainage for deep infection at the bone implant interface. Classification of the reason for revision surgery is as follows: (1) Implant failure (2) Superficial or deep infection ; (3) Avascular necrosis; (4) Hip instability; (5) Hip dislocation; (6) Open wound; (7) Painful hardware; (8) Intractable pain due to wear of the acetabulum; (9) Peri-prosthetic femur fracture; and (10) Nonunion. Other classifications will be used if applicable. Planned revision surgeries will not be considered study events (i.e., technical malreduction requiring early revision). Criteria for the diagnosis of nonunion will include a failure of the fracture to progress towards healing for at least 2 months on consecutive radiographs. This will be evident as a persistent fracture line on radiograph, continued pain with hip range of motion, and the inability to weight-bear without pain. Avascular necrosis will be defined as a process that is characterized pathologically by bone marrow ischemia and eventual death of trabecular bone. Infection will be classified according to the Center for Disease Control Criteria [29].

Our choice of a 24 month follow-up period is dictated by the following 2 factors: (1) We have established a consensus among participating surgeons that the decision to re-operate on the hip fracture would occur within the first 24 months following surgery in all, or virtually all, patients and (2) Previous studies have reported 100% of revision surgeries occurring between 2 and 12 months for undisplaced fractures and 70-100% in 24 months for displaced fractures. Although nonunion and avascular necrosis may be present after 24 months, previous studies suggest that 70-98% of revisions due to nonunion and avascular necrosis occur within 24 months [30,31]. Thus, we can expect that nearly all the revision surgeries will occur within 24 months.

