### Statistical plan

#### *Sample size determination*

The determination of sample size is based upon a comparison for the primary outcome (revision surgery) of the sliding hip screw versus multiple cancellous screw groups. All statistical hypotheses will be assessed using 2-sided significance tests. Alpha levels of 0.05 have been chosen for the primary and 0.01 for the secondary outcomes. Previous studies have reported revision surgery rates in hip fracture patients that have ranged from 0-44% [39-41], with a weighted pooled risk of 22.7% (95% CI: 19.6-25.8%). In a pooled estimate of 5 RCTs comparing sliding hip screw fixation with multiple screw fixation in patients with displaced or undisplaced hip fractures, sliding hip screws reduced the risk of revision by 32% (95% CI: 3-53%, p = 0.04, Q = 5.3) [22,42-45]. The sample size calculation reflects the proposed primary analysis, which will use the Cox proportional hazards model, and is based on methods described by Collett [46]. The goal is to calculate the required number of patients that will yield a sufficient number of outcome events (revision surgeries) in order to have adequate statistical power for a given size of treatment effect. This was done by taking into account the anticipated revision surgery rates in the multiple cancellous screw group, the postulated relative risk reduction with sliding hip screws, and the rates of mortality and loss to follow-up. Because some of these inputs are expected to change over the two year period of follow-up, the expected number of person-years of follow-up and the expected numbers of study events in each group were calculated initially for the first year of follow-up (year 1). The calculations were then repeated for the second year of follow-up (year 2), after having estimated the number of patients in each group who would survive, be event-free, and available for continued follow-up at 12 months post-randomization.

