The relative risk reduction was estimated to be 25% [43]. The decision to use a 25% annual event rate in the cancellous screws group for year 1 was based upon the previous literature [25,47] and compelling preliminary aggregate data (blinded to allocation) from our pilot study. Informed by the pilot study, annual mortality rates of 15% and losses to follow-up of 5% were assumed for each group. The annual event rates by group were converted into equivalent hazard rates, assuming for simplicity that the hazard rate would be approximately constant over year 1. It was calculated that approximately 58% and 63% of the group receiving cancellous screws and the group receiving sliding hip screw fixation would be event-free and available for further follow-up at the start of year 2. It was assumed that the revision rate would fall to one-third of its initial value during year 2 of follow-up (i.e., about 10% in the cancellous screws group), that the annual mortality rate would be 10%, and that there would again be 5% of patients lost to follow-up. The sample size was also increased to allow for an estimated combined 6.8% crossover rate from the assigned to the alternate treatment, based on our pilot data.

These assumptions lead to a required total sample size of 1,441 patients, who will yield an expected number of 353 outcome revisions. For convenience, the target number of patients was rounded to 1,500. Table 2 shows the study power for a sample size of 1,500 patients (750 per group) and a range of possible values for the initial revision rate and the relative risk reduction, on either side of the central assumed values. It demonstrates that with the chosen sample size of 750 per group, there will be a high likelihood of detecting a RRR of 25% or greater across the plausible range of revision surgery rates, and moderate power for slightly lower effect sizes.

**Table 2 T2:** Estimated study power for 750 patients per treatment arm (N = 1500)

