**Baseline risk**					
**(Year 1)^**	**Relative risk reduction**				
	**10%**	**15%**	**20%**	**25%**	**30%**
**20%**	15.9%	30.8%	50.5%	70.5%	**86.1%**
**25%**	19.6%	38.7%	61.6%	**81.5%**	**93.5%**
**30%**	23.6%	46.8%	71.7%	**89.3%**	**97.4%**
**35%**	28.2%	55.2%	**80.3%**	**94.5%**	**99.1%**
**40%**	33.3%	63.6%	**87.3%**	**97.5%**	**99.7%**

*Number of patients per treatment arm, alpha = 0.05.

^Year 2 risk is 1/3 that of year 1.

Bold numbers indicate statistical power range for this study.

After 589 patients completed study follow-up, event rates were obtained and used to inform power analyses for a reduced sample size of 1,000 patients. A sample size of 1,000 patients was used in order to obtain a balance between feasibility of completing recruitment within a reasonable timeline and obtaining a sample size that will support plausible hypotheses of treatment effect and baseline event rates. Based on event rates calculated from the first 589 patients who completed the study, a 15.5% annual event rate was used for year 1 and a 27.2% annual event rate was used for year 2. Based on the data from the completed patients, it was assumed that the annual mortality rate would be 11.0% (year 1) and 18.2% (year 2) and that there would be a 12.2% (year 1) and 5.9% (year 2) loss to follow-up. The sample size was again increased to allow for an estimated combined 6.8% crossover rate from the assigned to the alternative treatment. Table 3 shows the study power for a sample size of 1,000 patients (500 per treatment group) and a range of possible values for the initial revision rate and the relative risk reduction, on either side of the central assumed values. It demonstrates that with a sample size of 500 per group, there will be a likelihood of detecting a RRR of 30% or greater across the plausible range of revision surgery rates, and moderate power for slightly lower effect sizes.

**Table 3 T3:** Estimated study power for 500 patients per treatment arm (N = 1,000)

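### The treatment-by-displacement test uses logistic regression while the primary analysis and the subgroup power tables are time-to-event: a low-severity inconsistency that one sentence would remove

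*Protocol article*

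**What the plan says.** - Primary study endpoints: "The primary study endpoint is re-operation within 24 months post initial surgery".
- Primary analysis: for time to revision, "a Cox proportional hazards model will be used with the following covariates that are included in the minimization procedure". Displacement is one of those covariates, and treatment is tested by likelihood ratio. The Secondary analysis section also uses Cox models, for mortality and the fracture-related events.
- Sample size determination: "The sample size calculation reflects the proposed primary analysis, which will use the Cox proportional hazards model".
- Subgroup analyses: "The analysis plan is to fit logistic regression models and include treatment by subgroup interactions". The stated aim is to see whether the size of the treatment effect differs between displaced and undisplaced fractures. The section gives no reason for leaving the Cox model. It supports the analysis with Tables 4 and 5, whose rows are year-1 risks with a year-2 risk of one third.
- Sample size determination, revised assumptions: annual mortality of 11.0% and then 18.2%, and "there would be a 12.2% (year 1) and 5.9% (year 2) loss to follow-up".

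**The concern.** The effect the trial will report is a hazard ratio from a model that uses each patient's time at risk. The subgroup test is meant to ask whether that effect depends on displacement, but the named model has a yes/no outcome at 24 months.

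Two things follow. First, a patient lost at month 8 without revision contributes eight months to the Cox model. In the logistic model the same patient must be left out or counted as never revised. Second, the interaction becomes a ratio of odds ratios. One hazard ratio shared by two subgroups with different baseline risks gives two slightly different odds ratios, so a non-null interaction on one scale can be null on the other.

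This is the trial's only planned subgroup analysis, so a reader will want to set its result directly beside the primary hazard ratio.

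**Working it through.** **1. Which model lies behind Tables 4 and 5.** Inputs from Sample size determination (original assumptions): year-1 risk 25%, relative risk reduction 25%, year-2 risk one third of year 1, death 15% then 10%, loss 5% then 5%, crossover 6.8%, two-sided alpha 0.05. Each annual rate r becomes a hazard −ln(1−r), and the three exits compete within each year.

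- Hazard ratio = ln(1−0.1875)/ln(1−0.25) = 0.722.
- Expected events with 500 per arm: 136.5 + 103.7 = 240.2. Reduced for crossover: 240.2 × (1−0.068)² = 208.7.
- z = |ln 0.722| × √(208.7/4) = 2.35, so power = Φ(2.35−1.96) = 65%.

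| Table | Patients per arm | Computed | Stated |
|---|---|---|---|
| 4 | 500 | 65.4% | 64.5% |
| 5 | 250 | 38.4% | 37.8% |
| 2 | 750 | 82.2% | 81.5% |

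The subgroup tables are therefore Cox/log-rank power within each subgroup. They are not power for a logistic model, nor for an interaction.

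**2. How many patients leave unrevised before 24 months (cancellous-screw arm).** Revised rates: revision 15.5% then 27.2%, death 11.0% then 18.2%, loss 12.2% then 5.9%.

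- Year 1: hazards 0.1684 + 0.1165 + 0.1301 = 0.4151. Share leaving = 1−exp(−0.4151) = 34.0%, split in proportion to the hazards: revision 13.8%, death 9.5%, loss 10.7%.
- Year 2: 66.0% remain. Hazards 0.3175 + 0.2009 + 0.0608 = 0.5792. Share leaving = 0.660 × (1−exp(−0.5792)) = 29.0%: revision 15.9%, death 10.1%, loss 3.1%.
- Two-year totals: revision 29.7%, death 19.6%, loss 13.7%, followed and unrevised 37.0%.

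The same steps with the original rates, on which Tables 4 and 5 rest, give revision 27.3%, death 18.4%, loss 6.8%.

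**3. What the coding does to the 24-month risk (revised rates).**

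| Handling of unrevised deaths and losses | Estimated risk |
|---|---|
| Both coded event-free | 29.7% |
| Losses dropped, deaths event-free | 29.7/(100−13.7) = 34.4% |
| Both dropped | 29.7/(29.7+37.0) = 44.5% |
| Net risk at the stated rates | 1−0.845×0.728 = 38.5% |

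**4. What the change of scale does to the interaction.** Baseline risks are the plan's 30.2% (displaced) and 20.4% (undisplaced). Assumptions: two thirds of patients displaced; unadjusted models; test at two-sided 5%; equal, non-informative death and loss hazards across arms. The two risks were read as net 24-month risks with the revised rates (N=1,000), and as year-1 risks with the original rates (N=1,500). All three codings of step 3 were tried.

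| Scenario | Cox | Logistic, across codings |
|---|---|---|
| Common hazard ratio 0.75, revised rates: subgroup effects | 0.75 and 0.75 | odds ratios 0.71–0.73 displaced, 0.73–0.74 undisplaced |
| Common hazard ratio 0.60–0.75, either set of rates: ratio of effects | 1.00 | 0.97–0.99 |
| Same: rejection rate | 5.0% | 5.0–5.1% |
| Common hazard ratio 0.70, death and loss shifted 30% in opposite directions between subgroups: ratio of effects | 1.00 | 0.975–0.999 |
| True interaction (assumed hazard ratios 0.6 and 1.0), N=1,000: power | 33.7% | 33.0–33.6% |
| Same, N=1,500: power | 61.8% | 61.1–61.7% |

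Only an assumed contrast far outside the plan's figures (risks of 60% and 15%, common hazard ratio 0.6) moves the result visibly: ratio of odds ratios 0.83 to 0.93, rejection 5.4% to 7.0%.

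**The case against.** The strongest reply is that the endpoint is worded as an event within 24 months, which is naturally binary, and that the Primary analysis section itself also promises absolute rates, absolute risk reduction and number needed to treat. A patient who dies unrevised has had no re-operation in the window, so counting that patient as event-free gives a legitimate 24-month risk. Cox regression has its own difficulty, because it censors those deaths. The coding of deaths and losses may sit in an analysis plan that is not shown. The Study follow-up section limits unknown status by exhaustive tracing and, with approval, by chart review and telephone contact. All of this stands.

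It also answers two stronger readings. Adding deaths and losses (19.6% + 13.7% = 33.3%), a reader might infer that the logistic model mishandles a third of patients. The document does not say how they are coded, and the larger part are deaths, for which the 24-month outcome is known. Only the losses lack an outcome. A reader might also take the loss as 1−0.878×0.941 = 17.4%, but that ignores earlier exits by death or revision; the consistent figure is 13.7%. Finally, a reader might infer that the interaction test is invalid. Step 4 shows that at the plan's own risks it is not.

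The reply leaves the mismatch itself in place. The logistic model is a stated choice and not an omission, no reason is given for it, and the power tables beside it belong to another model.

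**Conclusion.** The point holds as a low-severity matter of consistency. The logistic interaction departs from the Cox model used for the primary analysis and from the time-to-event basis of Tables 4 and 5. It cannot use the partial follow-up of about 14% of the cancellous-screw arm (revised rates) or about 7% (original rates), and it treats deaths, about 18% to 20%, under a different estimand. The interaction is reported on a scale other than that of the primary result, but the shift is only about 1% to 3%, with error rate and power almost unchanged.

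The sizes rest on constant hazards within each year and on death and loss that are non-informative and equal across arms. Loss related to impending revision could make the coding matter more, but the document gives no figures on that.

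**What to change.** Replace the logistic sentence in Subgroup analyses with: the treatment-by-displacement interaction will be tested by likelihood ratio in the primary covariate-adjusted Cox model, with the baseline hazard stratified by displacement; hazard ratios with 95% confidence intervals will be reported for each subgroup. If displacement stays as an ordinary covariate, check proportionality between fracture types. The Primary study endpoints section gives reason for this: it cites earlier studies with all revisions in undisplaced fractures between 2 and 12 months, but only 70% to 100% within 24 months in displaced fractures.

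Keep the logistic model, if wanted, as a sensitivity analysis with a statement of how deaths and losses are coded.

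The cost is a sentence or two of wording, with the same data. There is a small downside: the Cox version assumes proportional treatment hazards within each subgroup and censors deaths, whereas a 24-month binary model needs neither. The logistic sensitivity analysis covers that.

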## Background

Hip fractures are a common type of fragility fracture that afflict 293,000 Americans (over 5,000 per week) and 35,000 Canadians (over 670 per week) annually [1,2]. The prevalence of hip fractures is likely to exceed 500,000 annually in the United States and 88,000 in Canada over the next 40 years [3,4]. The estimated annual health care costs will reach a staggering $17 billion in the United States [5] and $650 million in Canada [6,7]. Hip fractures are associated with a 30% mortality rate at 1 year [8] and profound temporary and sometimes permanent impairment of independence and quality of life [9,10]. The disability-adjusted life-years lost as a result of hip fractures ranks in the top 10 of all cause disability globally [3].

Intracapsular fractures (also known as femoral neck fractures) may be either undisplaced or displaced. Internal fixation, in which a mechanical implant fixes the two segments of bone together, is the best way to manage undisplaced fractures [11] and, depending on patient characteristics and surgeon preference, can be used to manage displaced fractures as well [12].

Complications of internal fixation include avascular necrosis of the femoral head as well as early implant failure and nonunion [13,14]. Approximately 30% of surgically treated hip fractures require revision surgery [15-17]. These revisions are associated with a large burden of morbidity and appreciable mortality. Even patients who do not require revision surgery may have long term functional limitation due to soft tissue damage at the time of surgery.

The most popular approaches to internal fixation include multiple cancellous screws or a single compression screw and side plate (i.e., sliding hip screws). Both approaches have strong physiologic rationale and ardent advocates; however, there is no consensus regarding the optimal approach for management of intracapsular hip fractures [12].

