### Surgical management of hip fractures

Bhandari and colleagues contacted 442 surgeons in an international survey [12] to explore surgeons’ opinions regarding internal fixation for femoral neck fractures. For undisplaced femoral neck fractures, 92% of surgeons preferred internal fixation. Despite the evidence suggesting the superiority of sliding hip screws, 90% of surgeons preferred cancellous screws. In displaced hip fractures, 25% of surgeons preferred internal fixation when compared with arthroplasty; and of those who preferred internal fixation, 68% preferred cancellous screws.

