### Eligibility criteria

Eligible patients will meet all the following inclusion criteria: (1) Men or women aged 50 years and older (with no upper age limit); (2) Fracture of the femoral neck confirmed with anteroposterior and lateral hip radiographs, computed tomography, or magnetic resonance imaging (MRI); (3) Operative treatment of displaced fractures within 4 days of presenting to the emergency room, or operative treatment of undisplaced fractures within 7 days of presenting to the emergency room; (4) Patient was ambulatory prior to fracture, though they may have used an aid such as a cane or a walker; (5) Anticipated medical optimization for operative fixation of the hip; (6) Provision of informed consent by patient or a legally appointed representative; (7) No other major trauma (defined as an Injury Severity Score >16); and (8) Low energy fracture, in the judgment of the attending surgeon.

We will exclude patients meeting any of the following criteria: (1) Patients not suitable for internal fixation (i.e., severe osteoarthritis, rheumatoid arthritis, or pathologic fracture); (2) Associated major injuries of the lower extremity (i.e., ipsilateral or contralateral fractures of the foot, ankle, tibia, fibula, knee, or femur; dislocations of the ankle, knee, or hip; or femoral head defects or fracture); (3) Retained hardware around the affected hip; (4) Infection around the hip (i.e., soft tissue or bone); (5) Patients with disorders of known bone metabolism except osteoporosis (i.e., Paget’s disease, renal osteodystrophy, osteomalacia); (6) Patients with a history of frank dementia that would interfere with assessment of the primary outcome (i.e., revision surgery at 24 months); (7) Likely problems, in the judgment of the investigators, with maintaining follow-up (i.e., patients with no fixed address, report a plan to move out of town, or intellectually challenged patients without adequate family support); and (8) Exclusion of a patient because of enrolment in another ongoing drug or surgical intervention trial will be left to the discretion of the attending surgeon, on a case-by-case basis.

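### The two-thirds displaced share behind the subgroup power tables makes no visible allowance for selection into internal fixation; it is probably too high, and so is the stated power for displaced fractures

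*Protocol article*

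**What the plan says.** In Subgroup analyses, the article relies on a survey and on population-based Swedish data, which it says "suggests that two-thirds of all included fractures will be displaced". It concludes: "Thus, approximately 1,000 displaced fractures (500 per group) and 500 undisplaced fractures (250 per group) can be expected". Table 4 (displaced, 500 per arm) and Table 5 (undisplaced, 250 per arm) are built on those counts. From Table 4 the text concludes that a relative risk reduction (RRR) of 30% or more is detectable in displaced fractures.

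Three other places bear on the mix:

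- Both trial arms are internal fixation (Study design).
- The Background says that internal fixation is the best way to manage undisplaced fractures and, "depending on patient characteristics and surgeon preference, can be used to manage displaced fractures as well".
- Surgical management of hip fractures reports the only survey described: "For undisplaced femoral neck fractures, 92% of surgeons preferred internal fixation", and "In displaced hip fractures, 25% of surgeons preferred internal fixation when compared with arthroplasty".

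**The concern.** A patient can enter this trial only if the surgeon is prepared to fix the fracture internally. On the article's own survey, that is far more common for undisplaced than for displaced fractures. A displaced share that holds among all femoral neck fractures therefore shrinks among those that are fixed. The article shows no step that allows for this.

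Two things depend on it. The first is the detectable-effect claim for displaced fractures, which needs 500 patients per arm. The second is the reading of the overall hazard ratio, which averages over whatever mix is enrolled. If displaced fractures are a smaller part of the trial than planned, the overall estimate says less about them than the plan suggests.

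**Working it through.** **1. The plan's own counts.** 1,500 × 2/3 ÷ 2 = 500 displaced per arm; 1,500 × 1/3 ÷ 2 = 250 undisplaced per arm. Both match the text.

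**2. The plan's own power.** The article gives inputs but no formula, so this is a reconstruction. Inputs, from Sample size determination and the table footnotes:

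- two-sided alpha 0.05, year 2 risk one-third of year 1;
- mortality 15% then 10%, loss 5% in each year;
- 6.8% crossover, taken as multiplying ln HR by 1 − 0.068 = 0.932.

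Annual risks p become hazards −ln(1 − p). Events accrue under competing death and loss. HR = ln(1 − p(1 − RRR)) ÷ ln(1 − p). Power = Φ(0.932 × |ln HR| × √events ÷ 2 − 1.96).

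For 25% baseline risk and 30% RRR:

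- Two-year event probability, cancellous screws: 0.226 + 0.047 = 0.273.
- Two-year event probability, sliding hip screw: 0.158 + 0.036 = 0.194.
- ln HR = ln(0.669) = −0.402.
- At 500 per arm: 500 × (0.273 + 0.194) ≈ 234 events; 0.932 × 0.402 × √234 ÷ 2 − 1.96 = 0.91; power 81.8%. Table 4 prints 81.0%.

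At 30% baseline risk the same steps give 89.6%; Table 4 prints 88.9%. Across Tables 4 and 5 the method agrees within 1.4 points. One Table 4 cell (30% risk, 20% RRR) was left out: it repeats the 45.3% of the row above, where about 54-55% is computed. A second reconstruction (average person-years, ln HR × 0.966) agrees within 0.7 points. Ranges below span the two.

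**3. The share after selection.** Let d be the displaced share among all femoral neck fractures and f the proportion of displaced fractures that are fixed. Take 0.92 as the proportion of undisplaced fractures fixed.

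Share among fixed = d·f ÷ (d·f + (1 − d) × 0.92)

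| d | f | Displaced share among fixed |
|---|---|---|
| 2/3 | 0.25 | 0.1667 ÷ (0.1667 + 0.3067) = 35% |
| 60% | 0.25 | 29% |
| 75% | 0.25 | 45% |
| 2/3 | 0.40 | 47% |
| 2/3 | 0.50 | 52% |
| 75% | 0.50 | 0.375 ÷ (0.375 + 0.23) = 62% |

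With d = 2/3, displaced fractures are a majority only if f exceeds 46%, and two-thirds is kept only if f = 92%. With f = 25%, two-thirds after selection needs d = 88%.

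**4. Power at the survey-implied share, N = 1,500.** 1,500 × 0.352 ÷ 2 ≈ 264 displaced and 486 undisplaced per arm.

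| Stratum and effect | Baseline risk | Printed | At 35% displaced |
|---|---|---|---|
| Displaced, RRR 30% | 25% | 81.0% | 54-55% |
| Displaced, RRR 30% | 30% | 88.9% | 63-65% |
| Undisplaced, RRR 40% | 20% | 68.0% | 92-93% |
| Undisplaced, RRR 40% | 25% | 79.0% | 97% |

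The displaced result can be checked without a model: Table 5, at 250 per arm, prints 51.3% and 61.4% for a 30% RRR at 25% and 30% risk.

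At 47% and 52% displaced (about 349 and 391 per arm), the step 2 method gives 67% and 72% at 25% risk, and 77% and 81% at 30% risk.

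**5. Weight in the overall estimate.** With the article's risks of 30.2% (displaced) and 20.4% (undisplaced), displaced fractures supply (2/3 × 30.2) ÷ (2/3 × 30.2 + 1/3 × 20.4) = 75% of events under the stated mix. At 35% displaced they supply (0.352 × 30.2) ÷ (0.352 × 30.2 + 0.648 × 20.4) = 45%.

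**The case against.** **The source is not visible.** The text speaks of included fractures and names the survey as a co-source. A reader might infer that two-thirds was lifted straight from all femoral neck fractures. The words population-based make that plausible, but the denominator is not given, so it remains an assumption.

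**A surgeon's preference is not a patient share.** That 25% of surgeons prefer fixation does not mean that 25% of displaced fractures are fixed, and surgeons who join a fixation trial may fix more. This stands. A reader might conclude that the mix is inverted; the documents do not establish that, because a rate above 46% restores a displaced majority.

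**Eligibility does not state the filter.** The exclusion reads "Patients not suitable for internal fixation (i.e., severe osteoarthritis, rheumatoid arthritis, or pathologic fracture", which mentions neither displacement nor surgeon preference, and displaced fractures are expressly eligible. The selection follows from both arms being fixation and from the Background's account of practice, not from a written criterion.

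**The pooled risks prove nothing here.** It is tempting to note that a two-thirds mix of 30.2% and 20.4% gives 26.9%, above the overall pooled 22.7%. But at the stated lower limit for displaced fractures the mix gives 2/3 × 24.1 + 1/3 × 20.4 = 22.9%, and the pools may come from different studies. No case mix should be read from this.

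**The primary analysis is protected.** Tables 2 and 3 do not use the split. Displacement is a minimisation factor and a Cox covariate, and its interaction with treatment is to be tested. This also stands, but it does not repair the stated stratum sizes or the detectable-effect claim.

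**Conclusion.** The point holds in limited form. The two-thirds share is not supported by the article's own survey, is probably too high, and may be reversed. At 35% displaced and N = 1,500, power for a 30% RRR in displaced fractures is about 55-65% over baseline risks of 25-30%, against the 81.0-88.9% stated. With 40-50% of displaced fractures fixed it is about 67-81%; only the most favourable corner reaches 80%. Power for undisplaced fractures would improve.

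This rests on three assumptions: that two-thirds describes all femoral neck fractures, that preference rates approximate treatment rates, and that the event assumptions of Tables 4 and 5 apply. Confidence is moderate.

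The reduction to 1,000 patients is a separate problem. It lowers displaced power to 64-65% and 73-75% (25% and 30% risk) even with two-thirds displaced (333 per arm), and to 39-40% and 47-48% at 35% displaced (176 per arm). Those losses should not be attributed to the case mix alone. The primary analysis is not invalidated.

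**What to change.** 1. Replace the two-thirds assumption with the displaced/undisplaced split observed so far. Displacement is a minimisation factor, so it is recorded for each randomised patient and can be counted without unblinding.
2. Recompute Tables 4 and 5, and the detectable-effect statements drawn from them, from those counts. Do not presuppose that the strata swap; a count near one half would call for neither the present sizes nor their reverse.
3. If the Swedish figure is kept as background, state its denominator.
4. State that the overall estimate reflects the observed mix, and that conclusions on displaced fractures rest on the stratum estimate, its interval and the interaction test.

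The cost is a count from the randomisation system, two recomputed tables and revised wording. The stated power for displaced fractures will probably become less favourable. No patients are added.
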